### Secondary outcome measures

The secondary outcome measures will include the following. The pain-related outcomes mainly included the cumulative PCA consumption during the first 48 h after TKA and the amounts of rescue analgesic at 48 h after surgery. We will also evaluate the pain severity using the VAS score, NRS score, BPI score, and KOOS score. The function-related outcomes included knee range of motion (ROM), Knee Society Score (KSS) score, Western Ontario and McMaster Universities Arthritis Index (WOMAC) score, and physical activity [55]. These outcomes will be assessed by means of several questionnaires at multiple follow-up time points. Furthermore, we will also collect other parameters, including joint-associated problems, health-related quality of life, CSI score, depressive and anxiety symptoms, perceived improvement and arthroplasty-related expectations, and patient satisfaction (ordinal scale) [56].

### Patient characteristics

The following baseline descriptive data will be obtained: age, gender, height (cm) and weight (kg), body mass index (BMI), marital status, family status, education level, employment status, duration of OA pain symptoms, Kellgren-Lawrence (K-L) grade, OA pain-related medication consumption, ASA classification, smoking and alcohol consumption, disease history, comorbidities, history of drug use, and past health problems.

### TKA-related characteristics

The surgical procedure-related data include the type of anesthesia, surgical approach, type of implant, operation time, intraoperative and postoperative blood loss, and arthroplasty-related complications.

### Adverse events

All adverse events reported spontaneously by the patients or observed by the investigators or staff will be recorded. If any adverse event occurs, the doctor will provide the corresponding treatment to the patient. Meantime, the adverse events will be immediately reported to the primary investigator and ethics committee to decide if the patient needs to withdraw from the trial. Based on previous literature, the most common adverse events were decreased appetite, nausea and vomiting, fatigue, insomnia, constipation, and dry mouth, which could be well managed with i.v. ondansetron [32, 43, 44].

### Data collection and management

The demographic and baseline characteristic data will be collected by screeners when the patients are recruited and enrolled in this trial (Table 1). During the hospitalization and follow-up periods, the clinical outcomes, questionnaires, incidence of complications, and adverse events will be collected by an independent trained investigator and will be monitored by an independent Data Monitoring Committee. No additional participants will be included during the re-evaluation period. Personal data will be handled confidentially. Every participant will receive a unique code, and data of each patient will be collected under this unique code. A unique patient identification list will be used to link the data to the patient, and the key to the code will be safeguarded by the principal investigator. All source documents will be entered into the trial database (OpenClinica clinical trials software).

**Table 1 Tab1:** Demographic and preoperative clinical characteristics of the patients

Demographics	Placebo group	Duloxetine group	Blank control group
Age (yr)			
Gender, n (%)			
Male			
Female			
BMI (kg/m^2^)			
Marital status			
Family status			
Education level, n (%)			
Primary school			
High school			
Some college			
Technical degree/associate’s degree			
Bachelor’s degree			
Advanced/professional degree (MA, PhD, etc.)			
Employment status			
ASA status			
I			
II			
III			
Preoperative parameters			
Duration of OA pain symptoms			
Kellgren-Lawrence grade			
OA pain-related medication consumption			
Smoking consumption			
Alcohol consumption			
History of drug use			
CSI score			
VAS score			
NRS score			
BPI-pain severity score			
KOOS score			

*ASA* American Society of Anesthesiologists, *BMI* Body Mass Index, *BPI* Brief Pain Inventory, *CSI* Central Sensitization Inventory, *KOOS* Knee injury and Osteoarthritis Outcome Score, *MA* Master of Arts, *NRS* numeric rating scale, *OA* Osteoarthritis, *VAS* visual analogue scale

### Sample size

Sample size calculation was performed with the VAS score as the primary outcome measure. Based on the previous study, the smallest change score for the VAS score to be considered clinically relevant is 2 points (on a 0–10 scale) between the duloxetine group and the placebo group [32]. The power calculation is performed based on the VAS score difference using a two-sided hypothesis test at an alpha level of 0.05 and a power of 80 %, and a total of 38 participants is needed in each group [57–59]. Taking into account the possibility of 20 % violators or dropouts, we will include 50 patients in each group.

### Statistical analysis

Analyses will be performed using the IBM SPSS software (version 21.0, IBM Corp., New York, NY, USA). All outcomes measures will be assessed using both the ITT (intention-to-treat, all randomly assigned patients) and PP (per-protocol, patients who completed the trial without any protocol deviations) data sets. The missing value will be imputed by the last-observation-carried-forward (LOCF) method. For continuous variables and descriptive values, means ± standard deviations (SDs) will be reported. For the enumerative variables, frequency and corresponding percentage will be calculated. For the variables with a normal distribution, statistical comparisons between the groups will be made by using a *t*-test. For variables with a non-normal distribution or ordinal level, the statistical comparison will be made using the Mann-Whitney U test. Outcomes with a discrete distribution will be expressed as percentages and analyzed by the *chi*-squared test or Fisher’s exact test as appropriate. A *P* value < 0.05 is considered statistically significant.

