Based on previous research, for patients who are identified as having CS before TKA, supplementing perioperative duloxetine to the multimodal analgesic protocol may help to reduce postoperative pain and opioid consumption, improve the quality of recovery in terms of both emotional and physical functioning, without increasing the risk of adverse events [32, 43, 44]. However, at this time, there is insufficient clinical data to recommend routine use of duloxetine in patients with CS to ameliorate the unexplained postoperative pain after TKA. In order to tackle this knowledge gap, we designed this prospective randomized study to evaluate the efficacy and safety of preoperative screening and targeted duloxetine treatment of CS on residual pain compared with the care-as-usual control group. We hypothesized that perioperative duloxetine would reduce postoperative pain and analgesic consumption, and enhance postoperative functional recovery after TKA, without increasing the risk of adverse events in patients who are identified as having CS before TKA. We present the following article in accordance with the *Standard Protocol Items: Recommendations for Interventional Trials (SPIRIT)* reporting checklist [45].

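### The per-protocol set is applied to all outcome measures without exempting adverse events, so a per-protocol safety comparison would leave out patients withdrawn for harm

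*Protocol article*

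**What the plan says.** The Statistical analysis section gives one rule on analysis sets: "All outcomes measures will be assessed using both the ITT (intention-to-treat, all randomly assigned patients) and PP". The second set is defined as "PP (per-protocol, patients who completed the trial without any protocol deviations) data sets". No outcome is exempted, and neither set is named as the one on which conclusions rest.

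Safety is part of the question. The Background gives the aim as "to evaluate the efficacy and safety of preoperative screening and targeted duloxetine treatment of CS on residual pain", and the hypothesis includes a benefit "without increasing the risk of adverse events in patients who are identified as having CS before TKA".

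On harms, the Adverse events section says two things that matter here. Recording is complete: "All adverse events reported spontaneously by the patients or observed by the investigators or staff will be recorded". Each event is also "immediately reported to the primary investigator and ethics committee to decide if the patient needs to withdraw from the trial".

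**The concern.** Completing the trial is a condition of entry to the per-protocol set, and an adverse event is one of the routes by which a patient may fail to complete. Taken together, these make membership of the set depend on the safety outcome itself. An adverse-event rate calculated in it describes patients whose events, if any, did not end their participation.

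The selection is not neutral with respect to the hypothesis. If duloxetine causes more events, or its events lead to withdrawal more often, more affected patients are removed from that arm than from placebo. The per-protocol table then moves toward equal rates, which is what the trial hypothesises. Because the two sets stand side by side with no order of precedence, the plan does not say which result to believe if they disagree on safety.

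**Working it through.** **Inputs from the protocol article**

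- All outcome measures are assessed in ITT and in PP; PP means completers without any deviation (Statistical analysis).
- Withdrawal after an adverse event is possible and is decided for each patient (Adverse events).
- 50 patients per group, with 20% allowed for violators or dropouts (Sample size).
- No adverse-event rate and no rate of withdrawal for adverse events is given.

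**The plan's own figure.** The article gives no figure on this point to reproduce. The nearest is the allowance for losses: 38/(1 − 0.20) = 47.5, so 48, against the stated 50. The allowance covers 0.20 × 50 = 10 patients per group.

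**Does the safety comparison fall under the rule?** The section headed Outcome measurement opens the list of parameters to be collected, and Adverse events is among the headings that follow. The Statistical analysis section is the only analysis rule given, and it ends with chi-squared or Fisher's exact tests for discrete outcomes. Most named efficacy outcomes are scores, amounts or ranges, so adverse events are an obvious use for those tests. The natural reading is that the rule covers them.

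**Illustration with counts (all rates assumed).** Suppose any adverse event occurs in 20/50 = 40.0% on duloxetine and 15/50 = 30.0% on placebo, a difference of 10.0 points. Remove from numerator and denominator those who withdraw because of the event:

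| Withdrawn for an event (duloxetine, placebo) | PP duloxetine | PP placebo | PP difference | ITT difference |
|---|---|---|---|---|
| 3, 1 | 17/47 = 36.2% | 14/49 = 28.6% | 7.6 points | 10.0 points |
| 6, 1 | 14/44 = 31.8% | 14/49 = 28.6% | 3.2 points | 10.0 points |

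The assumed withdrawals (at most 6) lie within the 10 per group that the plan allows for.

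**General form.** Let p be the true event rate and w the share of patients with an event who withdraw because of it, with no other exclusions. Then

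PP rate = p(1 − w) / (1 − pw).

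With the same w in both arms:

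| Assumed true rates | ITT difference | PP, w = 25% | w = 50% | w = 75% | w = 100% |
|---|---|---|---|---|---|
| 20% vs 10% | 10 | 8.1 | 5.8 | 3.2 | 0 |
| 30% vs 15% | 15 | 12.6 | 9.5 | 5.5 | 0 |
| 40% vs 20% | 20 | 17.5 | 13.9 | 8.4 | 0 |

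For example, 30% vs 15% at w = 50% gives 0.15/0.85 = 17.6% and 0.075/0.925 = 8.1%, a difference of 9.5 points. At w = 0, PP equals ITT.

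**Limits of the direction.** The PP rate is below p in each arm whenever w is above 0. The difference depends on the scale:

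- With equal w, the risk difference shrinks when p₁ + p₂ − w·p₁p₂ < 1. This holds in every row above, where p₁ + p₂ is at most 0.6, but it can fail when events are very common in both arms.
- The PP odds are p(1 − w)/(1 − p), so equal w leaves the odds ratio unchanged. It falls only if w is higher on duloxetine.
- In the count example w is higher on duloxetine: 3/20 = 15% or 6/20 = 30%, against 1/15 = 6.7%. The odds ratio moves from (20/30)/(15/35) = 1.56 to (17/30)/(14/35) = 1.42 or (14/30)/(14/35) = 1.17.

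**The case against.** The strongest reply is that the same sentence also requires an ITT analysis of every randomised patient. Harmed patients stay in that set, and all events are recorded without restriction to completers, so the data for an unaffected comparison exist. This stands, and it confines the problem to the per-protocol comparison. A reader might infer that safety will be judged in completers only, or that the trial as a whole will understate the drug's risk. The article says neither.

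A second reply is that adverse events are not outcome measures in the sense of the rule. They are not listed under the primary or secondary outcome headings, and the Data collection section names them beside clinical outcomes as a separate item. This shows that the text is ambiguous, but it does not amount to an exemption. On this narrower reading the article would state no analysis for the safety half of its question.

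Third, an adverse event does not automatically end participation. The text has the investigator and ethics committee decide, and it expects the common events to be manageable. A reader might take every event as a route out of the set; only those that end in withdrawal, or in another protocol deviation, are.

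Fourth, a named safety set may be defined in a full protocol or analysis plan that is not shown. Its absence from a journal article is no fault, and none is claimed. The point concerns the rule that the article does state, which a safety set defined elsewhere would still have to be reconciled with.

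**Conclusion.** The point holds in limited form. As written, the rule produces a second safety comparison, of equal standing with ITT, from which patients withdrawn for an adverse event are excluded by definition. The per-protocol rates are too low in any arm where such withdrawals occur. The difference between arms tends to shrink toward the hypothesised absence of added risk, most clearly if events on duloxetine lead to withdrawal more often than events on placebo.

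The size of the bias is unknown, because the article gives none of the rates needed. The fall from 10 points to between 7.6 and 3.2 illustrates the mechanism under assumed rates and is not an estimate for this trial. The ITT difference stays at 10 points in both cases, provided events up to withdrawal are counted. This merits correction before analysis, because safety is a stated objective and the plan does not say which set decides.

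**What to change.** In the Statistical analysis section, limit the per-protocol set to efficacy and state the basis for safety. Suggested wording:

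> The per-protocol set will be used for efficacy outcomes only. Adverse events will be compared between the duloxetine and placebo groups in all randomised patients who took at least one capsule, counting every event up to and including any that led to withdrawal. Conclusions on safety will rest on this comparison.

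The ITT set would serve equally well if the investigators prefer not to introduce another population. If a full protocol or analysis plan already defines a safety set, the sentence should simply point to it.

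The cost is one or two sentences, with no new data and no additional patients. The downside is that reported adverse-event rates may look slightly less favourable than they would in a per-protocol table.

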### Perioperative care

All TKAs will be performed by the same orthopedic surgeon using the same approach. The routine perioperative analgesic strategy, including preemptive analgesia (celecoxib), intraoperative periarticular cocktail injection, postoperative patient-controlled analgesia (PCA) and celecoxib, and discharge medication (celecoxib). In case of patients suffering unbearable postoperative pain, morphine or other opioids will also be given, the opioid consumption would also be recorded and compared. In the duloxetine group, patients will receive a half-dose of preemptive duloxetine (30 mg/day) for a week before surgery, and a full-dose of duloxetine (60 mg/day) for six weeks after surgery. The maintenance dose (60 mg/day) of duloxetine was chosen based on previous publications [32, 43, 44, 50]. While patients in the placebo group and blank control group will receive placebo for the same period. All enrolled patients will receive the same standard preoperative publicizing and education, intraoperative type of anesthesia, postoperative care, and rehabilitation.

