### Follow‐up period

During hospitalization, the basic metabolic panel will be obtained once or more to monitor serum sodium level, as hyponatremia is a duloxetine-induced complication that may occur early on after duloxetine initiation. In our routine clinical practice, patients are advised to return to the outpatient clinic for follow-up evaluation at one, three, and six months after surgery and subsequently every one year after surgery. Thus, in this clinical trial, all of the patients will be followed up at one, three, and six months after surgery. If patients are unwilling or unable to return to the study center for evaluation, they will be interviewed via telephone. Both the hospital and outpatient follow-up evaluation will be conducted by an investigator who is blinded to the experimental groups.

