### Primary outcome measures

The primary outcome is the intensity of residual pain at six months after TKA. The perception of residual pain will be measured with the visual analogue scale (VAS), 11-point numeric rating scale (NRS), the sensory dimension of the Brief Pain Inventory (BPI), and the pain subscale of the Knee injury and Osteoarthritis Outcome Score (KOOS) at six months after surgery [51–54]. These questionnaires have been proven to be valid and reliable, and the results of these questionnaires will help to ascertain the robustness of our results. The key postoperative time point of six months was chosen as this is recognized as the first possible time point to evaluate the ‘success’ of TKA in clinical practice.

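### LOCF as the only missing-data method can put preoperative, in-hospital or on-drug scores into the six-month primary comparison and bias it in either direction

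*Protocol article*

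**What the plan says.** All of the following is in the Methods of the protocol article.

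- **Missing data** (Statistical analysis): "The missing value will be imputed by the last-observation-carried-forward (LOCF) method". No second method is named.
- **Analysis sets** (Statistical analysis): "All outcomes measures will be assessed using both the ITT (intention-to-treat, all randomly assigned patients) and PP", the latter being patients who completed without deviations.
- **Endpoint** (Primary outcome measures): "The primary outcome is the intensity of residual pain at six months after TKA".
- **Treatment** (Perioperative care): one week of drug before surgery, then "a full-dose of duloxetine (60 mg/day) for six weeks after surgery".
- **Visits** (Follow-up period): "all of the patients will be followed up at one, three, and six months after surgery", with a telephone interview for patients who cannot or will not attend.
- **Earlier scores**: baseline values are recorded (Randomization and allocation; Table 1). The pain scales also appear among the secondary outcomes, of which the text says "These outcomes will be assessed by means of several questionnaires at multiple follow-up time points".
- **Expected loss** (Sample size): "Taking into account the possibility of 20 % violators or dropouts". Adverse events are reported to the investigator and ethics committee "to decide if the patient needs to withdraw from the trial" (Adverse events).

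**The concern.** LOCF assumes that a patient's pain stays where it was at the last visit. The Background describes knee replacement as an operation meant to relieve pain, so scores should move from before surgery to six months. The study drug also stops well before the endpoint. A score taken before surgery, in hospital or on drug does not stand for off-drug residual pain at six months.

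The error cancels between arms only if the timing and amount of loss, and the change still to come, balance out. Otherwise the primary comparison absorbs the difference. It could create an apparent effect or hide a real one, and nothing in the stated analysis would show which had happened. LOCF also enters filled-in values as if they had been measured.

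**Working it through.** **Inputs from the protocol article.** Endpoint at 6 months; drug ends 6 weeks (about 1.5 months) after surgery, so the gap is 6 - 1.5 = about 4.5 months; visits at 1, 3 and 6 months plus baseline; target 2 points on a 0-10 VAS; two-sided alpha 0.05; power 80%; 38 evaluable and 50 enrolled per group; 20% allowance. The article gives no pain trajectory, no SD and no split of dropout by arm or visit, so those are assumptions below.

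**The plan's own figures.** 38 / (1 - 0.20) = 47.5, so 48; the plan's 50 is slightly more and leaves 50 x 0.80 = 40. The SD behind 38 is not stated; solving backwards, SD = 2 / [(1.960 + 0.842) x sqrt(2/38)] = 3.11. SDs of 2 and 3.11 are used below as a range.

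**What LOCF would carry to six months.**

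| Patient lost | Score carried | Drug status |
|---|---|---|
| before 1 month | preoperative, or in-hospital if one is recorded | not at a follow-up visit |
| after 1 month, before 3 months | 1-month | on drug |
| after 3 months | 3-month | off drug |

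**Formula.** Bias = sum over last visits k of share(k) x [mean at k - mean at 6 months] in the duloxetine arm, minus the same sum in the placebo arm. Positive is against duloxetine.

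**Main illustration.** Assumed mean VAS 6.5 before surgery, 4.0 at 1 month, 3.0 at 3 months and 2.5 at 6 months; no true six-month difference.

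- Case A: 15% of duloxetine and 5% of placebo patients are lost with the preoperative score carried, plus 5% of each arm last seen at 1 month. The 1-month terms cancel. Bias = (0.15 - 0.05) x (6.5 - 2.5) = **+0.40**, or 0.40/2 = 20% of the target.
- Case B: 20% of each arm is last seen at 1 month, and duloxetine has a transient 1.5-point benefit then (2.5 against 4.0). Bias = 0.20 x (2.5 - 4.0) = **-0.30**, or 15% of the target.

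**Second set of assumptions.** Placebo 6.5 / 4.5 / 3.0 / 2.5 at baseline, 1, 3 and 6 months. Under no true effect duloxetine differs only at 1 month (3.0). Under a true effect of -2 it is 2.5 / 1.5 / 0.5 at 1, 3 and 6 months. Rejection rates come from a simulated t-test with 50 per arm, between-visit correlation 0.5 and 20,000 runs.

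| True effect | Loss pattern | Bias | Rejection, SD 2 / SD 3.11 |
|---|---|---|---|
| 0 | 20% each, last seen at 1 month | 0.20 x (3.0 - 4.5) = -0.30 | 11% / 8% |
| 0 | 20% each, baseline carried | 0 | 5% / 5% |
| 0 | 20% each, last seen at 3 months | 0 | not run |
| 0 | duloxetine 30%, placebo 10%, baseline carried | 0.20 x 4.0 = +0.80 | 35% / 21% |
| -2 | 20% each, baseline carried | 0.20 x (6.0 - 4.0) = +0.40 | 79% / 57% |
| -2 | 20% each, last seen at 1 month | 0.20 x (2.0 - 2.0) = 0 | over 99% / 87% |

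The 30% against 10% row is a stress test; the documents do not suggest such an imbalance.

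**Standard errors in Case A.** Carrying values from other mean levels adds variance between strata: 2.06 in the duloxetine arm (overall mean 3.175) and 0.84 in placebo (mean 2.775).

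- SD 2: LOCF SE = sqrt[(4 + 2.06 + 4 + 0.84)/50] = 0.47. Complete cases (40 and 45 patients): sqrt(4/40 + 4/45) = 0.43.
- SD 3.11: LOCF sqrt[(9.67 + 2.06 + 9.67 + 0.84)/50] = 0.67. Complete cases: sqrt(9.67/40 + 9.67/45) = 0.68.

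The LOCF standard error is therefore not reliably smaller than that from complete cases.

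**The case against.** The case for leaving the plan alone has several sound parts.

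- **The bias is conditional.** A patient last seen at three months carries an off-drug score, and several patterns above give zero bias. A reader might infer that LOCF must distort this trial; the documents support only that it can.
- **The preoperative score may not be the one carried.** Follow-up period and Data collection and management both refer to evaluation during the hospital stay. An in-hospital score would be no better a stand-in for six-month pain, but Case A's 6.5 is then not the value used.
- **Telephone interviews** suit questionnaire pain scores and may keep loss low. They do not change how the remaining gaps are filled.
- **The 20% covers violators as well as dropouts**, so it is not a missing-data rate. Case B uses all of it as dropout.
- **Loss through intolerance in the duloxetine arm alone is tempting to infer.** The article does not establish it. The withdrawal decision applies to every arm under blinding, the Background cites an earlier trial in sensitized patients with no excess of adverse medication effects, and the hypothesis expects none. Unequal loss is a risk only.
- **It is also tempting to say that LOCF standard errors are too small.** Case A shows that this is not generally so.
- **Follow-up after stopping capsules.** A reader might infer that stopping study drug ends data collection. The article does not say so, and an article commonly leaves that detail to the full protocol. It carries no weight here.

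These points limit the size and certainty of the problem but do not make LOCF suitable. The article fixes the method, so this is not a gap left to an analysis plan. The per-protocol analysis is no safeguard, because it selects on completion.

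**Conclusion.** The point holds in conditional form. With LOCF as the only method, patients lost before the three-month visit would have a preoperative, in-hospital or on-drug score counted as six-month residual pain. That can bias the duloxetine-placebo comparison either way.

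In the main illustration the bias is +0.4 to -0.3 points, 15 to 20% of the 2-point target. It is zero in some patterns and larger only under dropout imbalances that the documents give no reason to expect. All of these sizes rest on assumed pain means and dropout shares. What rests on the document itself is the mechanism: a changing outcome, an endpoint about 4.5 months off drug, and a rule that holds scores constant. LOCF cannot be defended as conservative, because the sign is not known in advance. Its standard errors do not reflect imputation uncertainty, and their error can go either way.

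**What to change.** Change the missing-data sentence in Statistical analysis before unblinding.

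1. **Primary analysis of the two randomised arms.** Use a likelihood-based mixed model for repeated measures on the 1-, 3- and 6-month scores, with baseline pain, treatment, visit and treatment-by-visit, and report the six-month contrast. Alternatively, use multiple imputation with ANCOVA at six months.
2. **Sensitivity.** Both methods assume data missing at random and would not by themselves remove bias from informative loss. Add a delta-adjusted or tipping-point analysis. It should include patients with no postoperative score, who contribute nothing to a mixed model that has baseline only as a covariate.
3. **LOCF.** Drop it, or keep it only as a labelled sensitivity analysis.

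The cost is revised wording and modest extra analysis work, with possibly wider intervals. The visits are already scheduled, and no extra patients are needed on this account.

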### Randomization and allocation

After applying the selection criteria, the potentially eligible patients will be screened with the Central Sensitization Inventory (CSI) preoperatively, with a CSI score ≥ 40 indicating CS and a CSI score of < 40 indicating normal [46–48]. Patients with preoperative CS will be randomly allocated (1:1) to the duloxetine group or the placebo group by a computer-generated randomization list. After randomization, there will be a baseline assessment, such as patient demographics and baseline values for outcome measures. In addition, a group of patients who are assessed as normal will receive the placebo (as the blank control group). The hospital pharmacy will prepare indistinguishable capsules containing either duloxetine or placebo for the study. Randomization and allocation will be revealed only after the required number of subjects has been recruited and the data analysis has been completed.

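### The six-month pain scores are compared without their collected baseline values, by a test that depends on the observed distribution: valid, but less precise than it could be and not fixed in advance

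*Protocol article*

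**What the plan says.** All statements are in the Methods of the protocol article.

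- **Primary outcome measures:** "The primary outcome is the intensity of residual pain at six months after TKA". It is measured by VAS, NRS, the BPI sensory dimension and the KOOS pain subscale. No change from baseline is defined.
- **Statistical analysis:** "For the variables with a normal distribution, statistical comparisons between the groups will be made by using a" t-test. The alternative follows: "For variables with a non-normal distribution or ordinal level, the statistical comparison will be made using the Mann-Whitney U test". No covariate, regression model or other baseline adjustment is named. The section also says that means and SDs are reported for continuous variables.
- **Randomization and allocation:** after randomization, "there will be a baseline assessment, such as patient demographics and baseline values for outcome measures".
- **Data collection and management:** baseline data are collected at recruitment and enrolment. Table 1 lists preoperative VAS, NRS, BPI pain severity and KOOS as descriptive characteristics.
- **Sample size:** "the smallest change score for the VAS score to be considered clinically relevant is 2 points", two-sided alpha 0.05, 80% power, 38 per group, raised to 50 for 20% violators or dropouts. No SD is given.

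**The concern.** Two features of the stated analysis stand out.

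First, the preoperative value of each pain scale is on file but has no role in the comparison. Where preoperative pain predicts six-month pain, adjusting for it removes that part of the outcome variance and corrects the estimate for whatever baseline difference randomization leaves. With 38 to 50 patients per arm, that difference need not be small.

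Second, the test follows from the distribution of the variable or from its being called ordinal. The section does not say how normality is judged, or whether VAS and an 11-point NRS count as ordinal. The primary comparison could therefore be of means or of ranks, and the four primary scales could be tested by different methods. A Mann-Whitney P value does not test the mean difference on which the trial was powered.

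At stake are the width of the confidence interval and a primary analysis that is clear before the data are seen.

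**Working it through.** **Inputs.** From the Sample size section: difference 2 points, two-sided alpha 0.05, power 80%, 38 evaluable and 50 enrolled per group. Not stated, and so assumed: the VAS SD and the baseline to six-month correlation r.

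**1. The plan's own figure.** Without an SD, 38 per group cannot be reproduced directly. Solving the two-sample t-test for 80% power at n = 38 gives d = 0.651, that is SD = 2 / 0.651 = 3.07. A normal approximation gives 38 for SDs of 3.07 to 3.11. Dropout: 38 / 0.8 = 47.5, so 48, and the plan's 50 covers it.

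**2. Power with baseline adjustment.** ANCOVA multiplies the residual variance by 1 − r², so the effective effect size is 0.651 / √(1 − r²). Power comes from the noncentral t distribution with 2n − 2 degrees of freedom and noncentrality d√(n/2). The one degree of freedom spent on the covariate is ignored. The confidence interval narrows by 1 − √(1 − r²).

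| r (assumed) | 1 − r² | Interval narrower by | Power, 38 per group | Power, 50 per group |
|---|---|---|---|---|
| unadjusted | 1 | – | 80.0% | 89.7% |
| 0.1 | 0.99 | 0.5% | 80.4% | 90.0% |
| 0.2 | 0.96 | 2.0% | 81.6% | 90.8% |
| 0.3 | 0.91 | 4.6% | 83.5% | 92.2% |
| 0.4 | 0.84 | 8.3% | 86.3% | 94.0% |
| 0.5 | 0.75 | 13.4% | 89.9% | 96.1% |

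Both sample sizes are shown because 38 is the number the plan needs, while the intention-to-treat set with last observation carried forward could approach 50.

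**3. Chance imbalance.** The difference in baseline means has a standard error of √(2/n) baseline SDs: √(2/38) = 0.229. An imbalance of 1.96 standard errors is 0.45 SD. Taking the same SD at baseline and six months, it moves the unadjusted estimate by r × 0.45 × 3.07 points: 0.41 at r = 0.3 and 0.69 at r = 0.5, against a 2-point target. Imbalance that large or larger, in either direction, occurs in about 5% of trials.

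**4. Choosing the test from the data.** A check simulated 8,000 null trials per scenario at 38 per group, with a Shapiro-Wilk test in each arm followed by a t-test or Mann-Whitney test. Type I error was 5.3% for normal data and 4.7% for skewed 0–10 data.

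**The case against.** The strongest reply is that nothing here is invalid. Under 1:1 randomization the unadjusted test has its nominal error rate, and chance imbalance is already counted in its standard error. That stands. A reader might infer from the uncorrected imbalance or the data-driven choice of test that the trial would give biased results or too many false positives. The design and the simulation in step 4 do not support that.

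A reader might also infer that a rank test would leave no mean difference to set against the 2-point target. The Statistical analysis section reports means and SDs for continuous variables, so the group means would still be visible. What is missing is a commitment that the primary inference is about that difference.

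The size of the gain is also open to challenge. The correlation is not in the document, and the Background says that surgery has removed the pain source, so a weak correlation is possible. At r of 0.1 to 0.2 and 38 per group the gain is only 0.4 to 1.6 percentage points. At 50 per group and r of 0.3 to 0.5 it is 2.5 to 6.4 points, against 3.5 to 9.9 at 38. These limits stand.

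Two further replies are weaker. Covariates are often left to an analysis plan that is not shown here, but the article names the tests, so this concerns a stated choice. The sample-size section speaks of a change score, which leaves slight doubt whether baseline enters. However, neither the primary outcome nor the analysis section defines a change from baseline.

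**Conclusion.** The point holds as an improvement that should be made, not as an error that invalidates the trial. The stated analysis leaves collected baseline information unused and does not settle whether the primary test is of means or of ranks.

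The gain runs from negligible (r near 0.1) to about 10 percentage points of power at 38 per group or 6 at 50 (r = 0.5). These figures rest on an effect size back-solved from the stated sample size and on assumed correlations. The open choice of test does not depend on either assumption.

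A reader might take the baseline values as ready for use as they stand. The documents do not quite support that: one section places the baseline assessment after randomization and another places collection at recruitment and enrolment. Neither says that it precedes the first study dose, which is taken during the week before surgery.

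**What to change.** - Name as the primary analysis an ANCOVA of six-month VAS on treatment group (duloxetine versus placebo) with baseline VAS as covariate. Use the same model for NRS, BPI severity and KOOS pain, each with its own baseline. Apply it whatever a normality check shows.
- Report the adjusted mean difference with its 95% confidence interval against the 2-point target, with robust or bootstrap standard errors if residuals are skewed. Keep the Mann-Whitney test as a sensitivity analysis.
- State that the baseline is measured before the first study dose, and reconcile its timing between the sections on Randomization and allocation and on Data collection and management.

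The cost is a few sentences of analysis wording and the clarification of timing. No extra patients, visits or questionnaires are needed, provided the baseline is in fact taken before the first dose.
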